### Intervention

We will perform rTMS with the CCY-I magnetic field stimulator (Wuhan Yiruide Co., Ltd.), which can adjust the stimulation frequency from 0 to 100 Hz through a circular coil. Before the first treatment, single-pulse TMS will be administered to the primary motor cortex to elicit a discernible hand muscle response in at least three of five consecutive pulses to determine the resting motor threshold (RMT). The stimulation site of rTMS is the right DLPFC, which is located 5 cm anterior to the site of maximal stimulation of the first dorsal interossei in a parasagittal plane. To ensure better positioning of the TMS coil, we further use the scalp region used for F4 EEG electrode placement in the 10–20 International System (38, 39). The right DLPFC is known as one part of the socially related brain areas, plays a crucial role in the integration of goals and the reward system, has been found the weak responses in ASDs and selected for treating primary insomnia with good effects (23, 24). In addition, another study using 25% MT for the treatment of ASD found that it could alleviate sleep disturbances with little adverse effects (29). In this ongoing clinical trial, 1 Hz rTMS at 50% RMT (50 trains of 30 pulses, with a 3-s interval between each, leading to a sum of 1,500 pulses) will be applied over the right DLPFC. The treatment time will be determined according to the specific conditions of the subject, but the daily treatment time needs to be consistent (afternoon, the error cannot exceed 1 h). The operation process of the sham group will be the same as that of the rTMS treatment group, with no magnetic field passing through the skull. There will be no difference between the appearance and sound of the devices in the rTMS group and the sham group.

### Assessment

The assessments at baseline, after the 4-week treatment period, and the 4-week follow-up are summarized in Table 1.

**Table 1 T1:** Summary of the assessments.

	**Randomization**		
**Assessments**	**Baseline**	**After 4 weeks of rTMS treatment**	**Follow-up at 4 weeks**
Informed consent	√		
ADI-R	√		
ADOS	√		
Home-PSG	√	√	√
CSHQ	√	√	√
CARS	√	√	√
ABC	√	√	√
SRS	√	√	√
RBS-R	√	√	√
Blood	√	√	√

rTMS, repetitive transcranial magnetic stimulation; ADI-R, Autism Diagnostic Interview-Revised; ADOS, Autism Diagnostic Observational Schedule; PSG, polysmongraphy; CSHQ, Children Sleep Habits Questionnaire; CARS, Childhood Autism Rating Scale; ABC, Aberrant Behavior Checklist; SRS, Social Responsiveness Scale; RBS-R, Repetitive Behavior Scale-Revised. Home-PSG will be measured in two consecutive nights. Sleep diary will be record for at least 7 consecutive days before treatment, during the treatment and follow-up period. Adverse events report will be filled every day after randomization.

#### The clinical and sleep assessment

Through the self-designed questionnaire, demographic information, including race, sex, age, weight, height, past and current illnesses and medications, family income, the parent's educational level, mother's pregnancy disease, and childbirth, will be obtained.

##### Sleep studies

The sleep diary will be sent to parents to record their child's sleeping habits, including the child's bedtime, the time at which the child left his or her bed in the morning, the time to falling asleep, the number of times the child woke up and fell back asleep, and the total sleep time, for at least 7 consecutive days before treatment. These are also recorded during treatment and follow-up.

The Children Sleep Habits Questionnaire (CSHQ) is a parent-reported questionnaire (40). It consists of 41 questions that can reflect the common sleep problems in a typical recent week at 8 different levels: bedtime resistance, sleep onset delay, sleep duration, sleep anxiety, night waking, parasomnias, sleep-disordered breathing, and daytime sleepiness. A total score higher than 41 indicates sleep disturbance. The scale has adequate internal consistency, acceptable test-retest reliability, and acceptable validity to be widely used to evaluate sleep problems among different ages of ASD patients.

To objectively assess the change in sleep parameters and overcome the first-night effect, we will bring portable equipment to the patient's home for two consecutive overnight polysomnography examinations. Sleep data will be collected and scored *via* Somté PSG (Compumedics, OR). Measures will include six electroencephalographic (EEG) leads (F3-M2, F4-M1, C3-M2, C4-M1, O1-M2, O2-M1), two electrooculographic leads (ROC-M2, LOC-M2), 2 x Chin electromyography (EMG), 2 x Limb EMG, airflow from the pressure transducer and thermistor, thoracic and abdominal inductive RIP band, position, finger pulse oximetry, and electrocardiogram. Recording techniques and estimation of sleep parameters will follow the American Academy of Sleep Medicine guidelines (V.2.3).

##### Clinical assessment and questionnaires

The four scales below will be used to assess the changes in clinical symptoms from different aspects (severity, aberrant/repetitive behavior, social responsiveness) at baseline, after treatment and at the one-month follow-up (Figure 1).

The Childhood Autism Rating Scale (CARS) will be used to diagnose ASD by clinicians (41). Based on the levels of social, emotional, adaptive, communicative, and cognitive aspects, the CARS can divide ASD patients into three different severity groups. ASD severity will be graded by CARS as none to minimal symptoms (15–30 points), mild to moderate symptoms (30–37 points), and severe symptoms (38–60 points). We will use this scale to assess the severity of changes at the above three time points.

The Aberrant Behavior Checklist (ABC) will be used to evaluate the main ASD symptoms, including irritability, lethargy/social withdrawal, stereotypic behavior, hyperactivity/noncompliance, and inappropriate speech (42). ABC in Chinese has satisfactory psychometric properties and has been widely used in the evaluation of treatment efficiency.

The Social Responsiveness Scale (SRS) is a parent rating scale that is used to measure the severity or quantities of social impairment in clinical samples, including ASD (43). It consists of 65 items including five theoretical subscale scores (labeled social awareness, social cognition, social communication, social motivation, and autistic mannerisms). The total raw score ranges from 0 to 195, with higher scores indicating increased social impairment. We will use this scale to assess changes in social responsiveness.

The Repetitive Behavior Scale-Revised (RBS-R) is used to measure the various repetitive behaviors among individuals with ASD (44). There are 43 items rated for severity on a 4-point Likert scale. The total raw score ranges from 0 to 172, and higher scores indicate serious repetitive behaviors.

#### Untargeted metabolomics analysis

We will collect whole blood using a heparin sodium anticoagulant tube and perform plasma separation as soon as possible. Briefly, the sample will be centrifuged at 3,000 rpm at 4°C for 10 min, the upper layer will be collected, and 0.2 mL/tube will be transferred into 2 mL centrifuge tubes. After the sample is labeled, it will be quick-frozen in liquid nitrogen for 15 min and stored at −80°C. Then, the sample will be incubated on ice for 5 min and centrifuged at 15,000 rpm for 5 min at 4°C. Some of the supernatant will be diluted to a final concentration containing 53% methanol with LC–MS grade water. The sample will be subsequently transferred to a fresh Eppendorf tube and then centrifuged at 15,000 g for 10 min at 4°C. Finally, the supernatant will be injected into the LC–MS/MS system for analysis. The raw data files generated by UHPLC–MS/MS will be processed using Compound Discoverer 3.1 (CD3.1, Thermo Fisher) to perform peak alignment, peak picking, and quantitation for each metabolite. These metabolites will be annotated using the KEGG database (http://www.genome.jp/kegg/), HMDB database (http://www.hmdb.ca/), and Lipidmaps database (http://www.lipidmaps.org/).

### Outcomes

The primary outcome of this study will be the difference in sleep onset latency between baseline and the end of treatment. Secondary outcomes will be differences in other parameters derived from polysomnography, the sleep diary, CSHQ, CARS, ABC, SRS, RBS-R, and metabolomics analysis.

#### Safety outcomes

Family members will also be asked to complete an adverse event report every day, and this report will include information about potential side effects, including headache, nausea, vomiting, and seizures. If the above symptoms occur during treatment, treatment will be immediately stopped to see if these symptoms subside. If status epilepticus occurs, the patient will be sent to the emergency room for symptomatic treatment. Safety outcomes and treatment-related side effects will be assessed and reported in the publication.

#### Follow-up

Four weeks after the last rTMS or sham treatment, parents and patients will be asked to return for a reevaluation of symptoms using the above scale. The CSHQ and home-PSG will be then used to assess sleep quality. In addition, whole blood samples will be collected again.

### Data management

A standardized case report form (CRF) was developed for the current study. After the clinical symptoms of the patients are evaluated at the specified time points, the data will be entered into the Excel database immediately. To ensure the accuracy of the data, another researcher will double-check.

## Statistical analysis

We will use SPSS software version 26.0 (IBM Corp, Armonk, New York, US) to perform data analysis. Demographic and baseline data will be analyzed with standard descriptive statistics. Normally and non-normally distributed data will be presented as means (SDs) and medians (quartiles), respectively. The comparison of basic data between the rTMS group and sham rTMS group will be performed using Student's *t*-test, the chi-squared test, or the nonparametric test according to the data type. To verify the efficacy of our intervention, the final analysis will be conducted according to the intent-to-treat (ITT) principle, and missing data will be replaced by means of the last observation carried forward rules. Changes in quantitative variables over time (evaluation of the therapeutic effect of rTMS on variations in sleep latency) will be analyzed using random-effect models allowing us to take into account repeated measurements. Time (baseline, post, and 1-month follow-up) and group (rTMS or sham) effects will be estimated and tested, along the interaction with the group. According to the same strategy, changes in other quantitative variables over time will be investigated. To further analyze the relationship between the change in the parameter of sleep and clinical symptoms, logistic regression, general linear correlation or regression will be taken into consideration between various types of outcomes. The number and proportions of participants with side effects, adverse events, and serious adverse events will also be reported. All statistical analyses will be two-sided, and statistical significance will be set at p<0.05. For untargeted metabolomics analysis, principal component analysis (PCA) and partial least squares discriminant analysis (PLS-DA) will be performed in metaX (a flexible and comprehensive software for processing metabolomics data). We will apply univariate analysis (*t*-test) to calculate the statistical significance (*P* value). Metabolites with VIP > 1 and *P* value < 0.05 and fold change (FC)≥ 2 or FC ≤ 0.5 will be considered to be differential metabolites.

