**Method:**

This study is designed to be a double-blind, randomized, and sham-controlled trial with a target sample size of 30 participants (aged 3–13 years) diagnosed with ASD comorbid with insomnia. The intervention phase will comprise 20 sessions of rTMS or sham rTMS applied over the right dorsolateral prefrontal cortex (DLPFC) within four consecutive weeks. The effect of rTMS on insomnia and other symptoms of ASD will be investigated through home-PSG (two consecutive overnights), sleep diary, CSHQ, CARS, ABC, SRS, RBS-R, and metabolomics analysis at baseline and posttreatment. A follow-up assessment 1 month after the intervention will examine the long-term effects.

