### Sample size

Previous studies in patients with insomnia have shown that rTMS treatment can decrease sleep onset latency by at least 17.88–44.8 min (30, 31). According to previous studies, the minimally important difference of the primary outcome (sleep onset latency) is assumed to be 10 min (SD, 8.4 min) (32). To detect this difference with a two-sided significance level of 0.05 and a power of 80%, and account for the drop rate of 10% according to existing rTMS studies in autism (33, 34), a total of 30 participants will be included (PASS, version 15).

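### LOCF is prescribed ahead of a random-effects model that does not need it; it can bias the primary contrast in either direction and builds persistence into the 1-month result

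*Protocol article*

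**What the plan says.** The Statistical analysis section puts the final analysis on an intent-to-treat footing and adds that "missing data will be replaced by means of the last observation carried forward rules". Sleep latency is then to be analysed with "random-effect models allowing us to take into account repeated measurements". On the model terms it says: "Time (baseline, post, and 1-month follow-up) and group (rTMS or sham) effects will be estimated and tested", together with the interaction. The same strategy applies to the other quantitative outcomes. The section gives no reason for choosing LOCF.

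The primary outcome (Outcomes) is "the difference in sleep onset latency between baseline and the end of treatment". The secondary list begins with the other PSG parameters, so sleep onset latency is read here as a PSG measure. Table 1 schedules home-PSG at baseline, after 4 weeks of treatment and at the 4-week follow-up only.

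On the last visit the abstract says: "A follow-up assessment 1 month after the intervention will examine the long-term effects". The Sample size section allows for 10% dropout. The Inclusion/exclusion criteria section withdraws children for intolerance, adverse events or missed sessions. Under Trial status, data collection runs until 30 children have completed all sessions and the pre- and post-treatment measurements.

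**The concern.** PSG is done at three visits only, so LOCF acts in two ways.

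- **No post-treatment PSG.** The last observation is the baseline value, and the child enters the primary comparison with a change of exactly zero. Any improvement that the child would have shown, including improvement unrelated to the active stimulation, is erased.
- **Post-treatment PSG present, 1-month PSG absent.** The end-of-treatment value is copied forward, so the child is recorded as having kept the whole gain. Persistence is what this visit is meant to test.

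In both cases the model treats the copied value as a measurement, so the standard errors are not those of the data actually collected. A likelihood-based random-effects model needs none of this: children with incomplete visits contribute what was observed. With 15 children per arm, a few copied values can move the result.

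**Working it through.** **Inputs from the protocol article.** Difference 10 min, SD 8.4 min, two-sided 0.05, power 80%, dropout 10%, total 30 (Sample size); 1:1 allocation, hence 15 per arm (Randomization and blinding). Loss rates other than 10%, the change within each arm and the 1-month effects are assumptions.

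**The plan's own figure.** For a two-sample t-test with d = 10/8.4 = 1.19, power is 0.796 with 12 per arm and 0.829 with 13 per arm. So 13 per arm are needed; 13/0.90 = 14.4, rounded up to 15 per arm, gives 30. The stated total is reproduced. With 15 per arm and complete data, power is 0.88.

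**Formulas for LOCF at end of treatment.** Let an arm have true mean change c and proportion p lost before the post-treatment visit, at random.

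- Expected change after LOCF = (1−p)c
- Variance after LOCF = (1−p)·8.4² + p(1−p)c²

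Once LOCF has filled every visit, the group-by-time contrast is the difference in mean change, so the t-test on change scores stands in for the model. Powers are therefore approximate.

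**Planned loss, 10% in each arm.** The effect is 0.9 × 10 = 9.0 min whatever the change in the sham arm.

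- Changes −10 and 0: variances 63.5 + 9.0 = 72.5 and 63.5, pooled SD 8.25, power 82%.
- Changes −15 and −5: variances 63.5 + 20.25 = 83.8 and 63.5 + 2.25 = 65.8, pooled SD 8.65, power 79%.
- Observed children only: 15 × 0.9 = 13.5 per arm; power 83% for 13 versus 13 and 86% for 14 versus 14.

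**Unequal loss (assumed), changes −15 (active) and −5 (sham), true effect 10 min.**

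| Loss active / sham | LOCF effect | Power |
|---|---|---|
| 25% / 10% | 11.25 − 4.50 = 6.75 min | 51% |
| 25% / 5% | 11.25 − 4.75 = 6.50 min | 48% |
| 10% / 25% | 13.50 − 3.75 = 9.75 min | 87% |
| 5% / 15% | 14.25 − 4.25 = 10.00 min | 88% |

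For the first row, about 11 versus 14 observed children give 81% power.

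**No true effect, both arms improve by 10 min (assumed), 20% lost in one arm only.** The arm with losses shows 0.8 × 10 = 8 min and the other 10 min: a spurious 2-min difference. Simulated type I error is about 10% instead of 5%. Loss in the active arm counts against rTMS; loss in the sham arm gives a false benefit.

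**One month.** Suppose the end-of-treatment effect is 10 min, the true 1-month effect is f, and a proportion m of each arm misses only the 1-month visit. LOCF then gives (1−m)f + 10m.

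- f = 0: false benefit of 1.0 min at m = 10% and 2.0 min at m = 20%; simulated false-positive rates 5.7% and 9.0%.
- f = 5: 5.5 and 6.0 min instead of 5.

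**Likelihood fit to observed visits.** In the same kind of simulation (15 per arm, change SD 8.4) the estimates stayed within about 0.1 min of the truth at both visits, with loss completely at random and with follow-up loss depending on the post-treatment value (MAR).

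**The case against.** The strongest reply is that at the only loss rate the protocol article states, little happens. With 10% in both arms the primary estimate moves by 1 min towards no effect, which is conservative for a benefit claim, and power stays close to the planned 80%. The trial is described as a pilot, and the 1-month visit is not the primary time point. All of that stands, and it limits the severity.

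The completer rule under Trial status may also keep missing post-treatment values few, if children who withdraw are replaced. It gives less cover than it seems: withdrawn children kept under intent-to-treat would still be imputed, and the rule does not require the follow-up visit.

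MAR itself is uncertain when children are withdrawn for intolerance or adverse events. That is a fair caution about the likelihood model, but it is no argument for LOCF, which makes a more specific assumption: that the value freezes at the last visit.

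A reader might infer that the primary estimate is biased whenever loss differs by arm or either arm changes over time. That is too strong. Changes of −15 and −5 with 5% and 15% loss return exactly 10.0 min, and equal change with equal loss gives no bias. A reader might also infer that the trial is headed for about 50% power. Those figures need an assumed 25% loss in the active arm, two and a half times the planned rate, with much lower sham loss.

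**Conclusion.** The point holds as a should-fix. The protocol article fixes LOCF as the missing-data rule, so this is not a detail left open for a statistical analysis plan. The rule is unnecessary for the model chosen, it can bias the primary contrast in either direction depending on loss and change in each arm, and it treats copies as data.

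At the planned 10% equal loss the cost is small: 9.0 min instead of 10, with power about 79–82% when the sham arm changes by 0 to 5 min, against about 83% for 13 versus 13 observed children. Larger harm depends on assumed unequal loss: 6.75 min and 51% power in one pattern, or a spurious 2 min with about 10% type I error in another.

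At 1 month the rule assumes persistence. It leaves a false 1 to 2 min if a 10-min benefit has fully gone and 10 to 20% miss the visit. It does not follow that a lasting benefit will be manufactured: at 10% missing the false-positive rate is 5.7%, barely above nominal.

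**What to change.** Delete the LOCF clause and put in its place: *The primary analysis is the likelihood-based mixed model on all randomised participants, using all observed visits without imputation (missing at random). The primary estimate is the group-by-time contrast at the end of treatment.* LOCF may stay at most as a sensitivity analysis. Any analysis of departures from MAR can be left to the statistical analysis plan.

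The cost is wording only. The sample size stays at 30 and no further data are needed. Recruitment is under way, so the change should be made before unblinding; a switch of method afterwards would be open to challenge.

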### Randomization and blinding

For participant allocation, a computer-generated random list will be used, which is based on the permutation block method with a random number generator and allocated at a ratio of 1: 1. A research assistant concealed the allocation sequence using sealed, opaque envelopes that contain the treatment information (A or B) before officially entering the study. After completing the consent form and baseline measures, the corresponding envelope for a given participant ID will be given to the rTMS therapist prior to the first rTMS session. The rTMS therapist is the only person who determines the treatment method (rTMS or sham treatment) for A or B. Once the treatment information is decided, no change will be accepted. Others, such as study investigators, parents, patients and statistical analysts, will be completely blinded to the treatment condition. Any adverse effects or body discomfort will be recorded after each rTMS treatment session. The aforementioned individuals will be unblinded to information about the treatment only when a participant experiences serious adverse events, and then an independent investigator will reveal the current treatment of this participant.

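### The primary endpoint is the change in sleep onset latency to end of treatment, but the analysis lists tests of time, group and a three-visit interaction without naming the week-4 between-arm contrast as the primary test

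*Protocol article*

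**What the plan says.** **Endpoint.** Protocol article, Outcomes: "The primary outcome of this study will be the difference in sleep onset latency between baseline and the end of treatment". Other polysomnographic parameters are listed as secondary, so the primary latency is evidently the home-PSG one.

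**Sizing.** Sample size: "the minimally important difference of the primary outcome (sleep onset latency) is assumed to be 10 min (SD, 8.4 min", with a "two-sided significance level of 0.05 and a power of 80" per cent. The plan will "account for the drop rate of 10% according to existing rTMS studies in autism", and "a total of 30 participants will be included (PASS, version 15". Randomisation is "allocated at a ratio of 1: 1". The section names no test and does not say whether 8.4 min is the SD of the change or of a single measurement.

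**Analysis.** Statistical analysis: changes over time, with sleep latency as the stated case, "will be analyzed using random-effect models allowing us to take into account repeated measurements". It then adds: "Time (baseline, post, and 1-month follow-up) and group (rTMS or sham) effects will be estimated and tested, along the interaction with the group". Baseline is therefore one of three levels of time, that is, a response. No baseline covariate is mentioned. All tests are two-sided at 0.05.

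**The concern.** The endpoint is a single between-arm comparison at one visit. None of the three listed tests, taken as written, is that comparison:

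- The **time** effect says nothing about rTMS versus sham.
- The **group** main effect averages over all three visits, including the one before treatment, where randomisation makes the arms equal in expectation.
- The **interaction** over three visits has 2 df and also responds to the 1-month visit, which lies outside the primary endpoint.

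With 30 children, the choice among these p-values can decide the conclusion, and the section gives no rule for choosing. A claim on the primary endpoint could then rest on a test that answers a different question. The model also spends baseline on a free group difference, although randomisation allows it to be used more efficiently.

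**Working it through.** **1. The plan's own figure.** Difference 10 min, SD 8.4 min, two-sided 0.05, 80% power.
- Normal approximation: 2 × (1.960 + 0.842)² × 8.4² / 10² = 11.1, so 12 per arm.
- Two-sample t-test: 12 per arm gives 79.6% and 13 gives 82.9%, so 13 per arm. Then 13 / 0.90 = 14.4, so 15 per arm, total 30.

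The stated 30 is reproduced as a 1-df two-arm comparison.

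**2. Dilution in the group main effect.** The between-arm difference averaged over baseline, week 4 and 1 month is:
- effect fully persists: (0 + 10 + 10) / 3 = 6.7 min
- half remains: (0 + 10 + 5) / 3 = 5.0 min
- effect gone by 1 month: (0 + 10 + 0) / 3 = 3.3 min

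**3. Power of each test.** Assumptions not in the document: 8.4 min is the SD of change, compound symmetry, r = 0.3 to 0.7, and 27 children analysed (30 × 0.90), 14 versus 13.

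Let k = 1/14 + 1/13 = 0.1484. The single-visit variance is σ² = 8.4² / [2(1 − r)].
- *Week-4 change contrast:* SE = 8.4 × √k = 3.24 and 10 / 3.24 = 3.09. Power is 84% (25 df), or 86% with the model's pooled 50 df.
- *Week 4 adjusted for baseline:* the residual variance is σ²(1 − r²) = 8.4² × (1 + r)/2, which is 0.65, 0.75 or 0.85 of the change-score variance at r = 0.3, 0.5 or 0.7. At r = 0.5, SE = √(52.92 × 0.1484) = 2.80 and 10 / 2.80 = 3.57.
- *Group main effect:* the variance of a child's three-visit mean is σ²(1 + 2r)/3. At r = 0.5 this is 47.04, so SE = √(47.04 × 0.1484) = 2.64.
- *2-df interaction:* λ = Σ(d − mean d)² / [σ²(1 − r)k]. Here σ²(1 − r) = 35.28 for every r, so the denominator is 5.23. For differences (0, 10, 10) or (0, 10, 0), λ = 66.7 / 5.23 = 12.7. For (0, 10, 5), λ = 50 / 5.23 = 9.6.

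| Test | Fully persists | Half remains | Gone by 1 month |
|---|---|---|---|
| Week-4 change contrast | 84–86% | 84–86% | 84–86% |
| Week 4, baseline-adjusted (r = 0.3 / 0.5 / 0.7) | 95 / 92 / 88% | same | same |
| 2-df interaction | 88% | 77% | 88% |
| Group main effect (r = 0.3 / 0.5 / 0.7) | 89 / 68 / 40% | 67 / 44 / 25% | 36 / 23 / 14% |

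The adjusted row allows for chance baseline imbalance. The simpler formula that ignores it gives about 96% to 90%.

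**4. An effect at 1 month only.** With differences (0, 0, 10), λ is again 66.7 / 5.23 = 12.7. The interaction is significant in about 88% of trials although the primary endpoint is null; the week-4 contrast rejects in 5%.

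**5. Two chances at 0.05.** If either the group or the interaction test counted as success, independence gives 1 − 0.95² = 9.75%. Simulation gives 9.3% to 9.9%.

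**6. If 8.4 min is instead the single-visit SD** (13 per arm, same r): change contrast 69–97%, baseline-adjusted 85–98%, interaction 60–98%, group main effect 19–76%.

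**The case against.** The strongest reply is that the model is not wrong. The post-versus-baseline by group coefficient is exactly the between-arm difference in the primary endpoint, the section says effects will be estimated as well as tested, and it presents the model as the evaluation of rTMS on sleep latency. On this view only a label is missing, and an article may leave that to an analysis plan. The first part stands: the model is usable. The second does not fully answer the point, because the section goes beyond silence: it positively lists the tests and the levels of time, and the list omits the week-4 contrast.

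Other parts of the reply also stand:
- A reader might infer that the baseline data are wasted. They are not; they are used as in a change score. The loss against adjustment is about 2 to 11 power points here and depends on a correlation the document does not give.
- A reader might infer that the interaction is always the weaker test. At 88% it beats the unadjusted change contrast if the effect fully persists or fully vanishes. Half persistence is its low point.
- A reader might infer that the type I error is 10%. That needs an either-test rule, which the plan neither states nor excludes.
- Trial status says collection continues until 30 have completed treatment and the pre- and post-measurements. At 15 per arm, under the change-SD reading, even the interaction's low point is 82%.
- Study design and settings calls the trial a pilot, which lowers the stakes but does not settle which test answers the primary question.

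**Conclusion.** The point holds as a mismatch between the endpoint and the listed tests. The endpoint is one week-4 contrast; the analysis lists three other tests and no rule among them. The most damaging choice would be the group main effect, with power anywhere from 14% to 89%. The omnibus interaction has acceptable power (77% to 88%) but can be significant with no week-4 effect at all. The contrast already inside the model has about 84%, and baseline adjustment would raise this to about 88% to 95%.

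The power figures rest on 8.4 min being the SD of change, on compound symmetry, on 14 versus 13 children and on r between 0.3 and 0.7. The dilution to 3.3 to 6.7 min and the interaction's sensitivity to a 1-month difference do not depend on the SD or the correlation. A reader might conclude that the trial is mis-sized; the documents do not support that, since 30 is reproduced and is adequate for the week-4 contrast under the change-SD reading.

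**What to change.** State one primary test in the Statistical analysis section: the rTMS-minus-sham difference in home-PSG sleep onset latency at end of treatment. Estimate it from the mixed model with the post and 1-month values as responses, visit, group, group-by-visit, and baseline latency as covariate. Equivalently for this purpose, keep baseline as a response but constrain its mean to be equal across arms.

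Make the 1-month between-arm contrast secondary. State that no efficacy claim will rest on the group main effect, the time effect or the omnibus interaction of the model now described.

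The cost is a change of wording and one degree of freedom. No new data are needed, because Table 1 already schedules home-PSG at all three visits, and the sample size does not change. Recruitment is described as ongoing, so the choice should be recorded before unblinding.
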